**Figure 2 F2:**
[figure not shown]
Study shoe versions.

### Stratified randomisation

Participants will be randomised at a 1:1:1 ratio to one of the three treatment arms. A block randomisation (block size 12) will be performed. Randomisation will be stratified by sex, as the latter influences body mass. Based on data from previous studies, the study population is expected to include about 40% of women. A statistician (at Luxembourg Institute of Health) who is not involved in any other part of the study will provide two pre-established randomisation lists before the beginning of recruitment. The participant identification number will comprise of four digits: the first digit corresponding to the participant’s sex (1=female, 2=male), followed by three digits corresponding to the randomisation number. The study groups and shoes will be coded, and an IT developer will upload the randomisation lists to the data collection system. Then, the data collection system will provide the investigator in charge of the recruitment with a study group number for each participant, according to the randomisation lists. The investigator will upload the shoe number according to the shoe size chosen and study arm so that the electronic system will perform cross-validation. The investigators in charge of the recruitment, the follow-up and data quality check, and the participants will be blinded regarding the shoe version distributed. The shoe code will be broken after the completion of data analysis.

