### Intervention

The study shoes are prototypes derived from a model available on the market (Kiprun KS 500 2) and will be anonymised for the purpose of this trial. The soles of the shoes will be customised for the study. The three running shoe versions will have the same design, except for their cushioning properties at the rear and forepart of the shoe, which will differ by about 40% and 30%, respectively (figure 2). Nevertheless, cushioning properties will remain within the range of values of the shoes available on the market (linear equivalent stiffness: 40±5 to 60±5 and 60±5 to 80±5 N/mm, at the rear and forepart of the shoe, respectively). We expect a difference in shoe weight lower than 30 g between the three versions (for size 43). The difference in cushioning properties between shoe versions will be created by modifying the type of foam and the foaming process. A set of shoes (5 pairs per version, shoe size 43) will be tested for stiffness properties by the manufacturer according to a standardised protocol (Impact test: ASTM F1614, Procedure A)^26^ to provide accurate data on the technical specifications (stiffness and dissipated energy). The cushioning properties (linear equivalent stiffness) of the study shoe versions will be characterised as follows (see also figure 2): hard shoe version (‘Hard-Hard’—about 60±5 and 80±5 N/mm at the rear and forepart of the shoe, respectively), mixed shoe version (‘Soft-Hard’—about 40±5 and 80±5 N/mm) and soft shoe version (‘Soft-Soft’—about 40±5 and 60±5 N/mm). The main hypothesis will be tested by comparing the mixed shoe version with the hard shoe version, while the secondary hypothesis will be tested by comparing the soft shoe version with both the hard and mixed shoe versions.

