### Sample size

A sample size calculation for Cox regression was used to determine the number of participants needed for the study’s primary hypothesis. With an alpha of 0.05 and a power of 80%, an average injury rate of 30%,^28 29^ an expected HR=1.50 between groups, 33% of participants randomised to each shoe group and an expected drop-out rate of 10%, the total number of participants required is 1068 (ie, 356 participants per group).

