### Statistics

Descriptive statistics will be presented as mean and SD for normally distributed continuous variables, median and range for skewed continuous variables, and count and percentage for categorical data, respectively. Shock absorption properties of the three shoe versions will be compared using an analysis of variance while considering the measurement uncertainty of the mechanical test.

Injury incidence will be computed for each outcome as the number of injuries per 1000 hours of running exposure. Injury prevalence will be computed for each outcome and per week by dividing the number of participants who reported an injury by the number of respondents of that week. Average weekly prevalence will be calculated separately for each outcome for the main anatomic locations.

To investigate the effect of shoe version, body mass and other possible risk factors on injury risk, subdistribution HR (sHR) with 95% CIs for the event of interest will be calculated using Fine-Gray models to account for competing risk. The date of inclusion and date of injury or censoring will be basic data used to calculate the time at risk, expressed in hours spent running and defined as the time scale.^14^ Participants will be right-censored if lost to follow-up or at the end of the intervention period. Average running practice characteristics will be computed for each participant over their specific period of observation. The assumption of proportional hazards will be evaluated using log-minus-log plots and Schoenfeld’s global test. First, unadjusted sHR will be estimated for shoe versions, body mass and other potential risk factors, such as running training characteristics. Subsequently, the variables with a p value <0.200 and well-established potential confounders will be included in an adjusted model to determine whether the model is improved with further adjustment. The model that best fits will be determined based on the log-likelihoods. Stratified analyses will be performed to investigate if the effect of shoe cushioning on injury risk is modified by sex, body mass (using the median value of body mass as cut-off, independently in men and women) or Body Mass Index. Finally, mediation analysis will investigate if the effect of cushioning on injury risk is partially explained by cushioning perception (and comfort).

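### Randomisation is stratified by sex, but the stated model-building rule does not guarantee that sex is in the primary mixed-versus-hard comparison

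*Protocol article*

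**What the plan says.** Under Stratified randomisation, the protocol article states "Participants will be randomised at a 1:1:1 ratio to one of the three treatment arms", then "A block randomisation (block size 12) will be performed" and "Randomisation will be stratified by sex, as the latter influences body mass". Two lists are prepared in advance, one per sex, and "the study population is expected to include about 40% of women".

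The Intervention section fixes the primary contrast: "The main hypothesis will be tested by comparing the mixed shoe version with the hard shoe version".

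The Statistics section sets out the modelling in three steps, using Fine-Gray models:

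1. "First, unadjusted sHR will be estimated for shoe versions, body mass and other potential risk factors, such as running training characteristics".
2. An adjusted model takes in variables with p below 0.200, together with established potential confounders. None is named.
3. The final model is the best-fitting one, judged by log-likelihood.

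That section names sex in its stratified analyses of effect modification, including the sex-specific median cut-off for body mass. The Objectives list sex as an exploratory factor and possible moderator, and cite earlier work in which injury risk may differ between men and women. Nowhere is sex named as a fixed term or stratum of the mixed-versus-hard comparison.

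**The concern.** When allocation is balanced within strata, the analysis should normally reflect those strata. If sex predicts injury, a model that ignores it attributes to chance some variation that the design has already removed. The standard error is then a little too large, the test a little conservative, and the hazard ratio drawn slightly toward 1. The authors themselves expect that injury risk may differ by sex, so this is not a remote possibility.

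A design factor should also not depend on a screening p value or a fit criterion. Under the stated rule, the trial's own data can decide whether the main comparison matches the randomisation.

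**Working it through.** **Inputs from the article.** Sex strata, blocks of 12, 1:1:1 allocation and about 40% women (Stratified randomisation). Alpha 0.05, power 80%, injury rate 30%, HR 1.50 and drop-out 10% (Sample size). Alpha is taken as two-sided; the article does not say.

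**Reproducing the plan's figure.** For one pairwise contrast with equal arms, Schoenfeld's formula is events = 4(z₀.₉₇₅ + z₀.₈₀)² / (ln HR)². With 1.960, 0.842 and ln 1.5 = 0.405, this gives 191 events, or 96 per arm after rounding up. Then 96/0.30 = 320 evaluable per arm, 320/0.90 = 356 randomised per arm, and 3 × 356 = 1068. This matches exactly. The calculation has no term for sex, so putting sex in the model leaves 1068 unchanged. Power at 2 × 96 = 192 events is 80.2%.

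**Balance.** A block of 12 holds 4 runners per arm. An unfinished block can therefore leave the mixed and hard arms at most 4 apart in each sex list at randomisation. Confounding of the shoe effect by sex is not the issue; matching the analysis to the design is.

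**Would the p-value route bring sex in?** Across three arms, 1068 × 0.90 × 0.30 ≈ 288 events are expected. With 40% women, the expected z for sex is √(288 × 0.40 × 0.60) × ln(sex HR) = 8.31 × ln(sex HR). It is compared with 1.282, the two-sided 0.200 limit. If entry rested on this route alone:

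| Assumed sex HR | Chance of entry |
|---|---|
| 1.0 | 20% |
| 1.1 | 33% |
| 1.2 | 60% |
| 1.3 | 82% |
| 1.5 | 98% |

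For a weak sex effect, the data decide.

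**What does omission cost?** The two-arm contrast was simulated with 640 evaluable runners (2 × 320), 40% women, 30% injured on average and allocation balanced within sex, with 10,000 runs per cell. Log-rank tests without and with sex strata were applied to the same data.

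| Assumed sex HR | Type I error, without / with | Power at HR 1.5, without / with |
|---|---|---|
| 1 | 4.4% / 4.4% | 80.0% / 80.0% |
| 1.5 | 5.0% / 5.2% | 78.9% / 79.3% |
| 2 | 4.3% / 4.8% | 78.9% / 80.0% |
| 3 | 4.1% / 5.1% | 76.9% / 79.7% |

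Monte Carlo standard errors are about 0.2 points for type I error and 0.4 for power. The difference within a row is more reliable than the level, because both tests use the same data. The power differences are 0.0, 0.4, 1.1 and 2.8 points.

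**Limits.** Log-rank tests stand in for the Fine-Gray model, there are no competing events, and follow-up is a fixed period instead of running hours.

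**The case against.** The strongest reply is that sex has a second way in. Established confounders join the adjusted model whatever their p value, and given the Objectives, sex is an obvious candidate. This stands. A reader might infer that sex is kept only if it passes the p-value screen; the text does not support that. But the article lists no confounder, and the closing choice by log-likelihood leaves room to remove a term. (The raw log-likelihood cannot fall when a term is added to a nested model, so this matters only if the choice works as a test or a penalised comparison, which the article does not specify.)

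A second reply is that sex is already analysed. That is true for effect modification, and a reader would be wrong to infer that the plan ignores sex. But separate results in men and women do not adjust the overall mixed-versus-hard contrast.

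A third reply is that a journal article may leave its covariate list to the full protocol or analysis plan. That is fair for the list itself. Here, though, the article states a concrete selection rule, and following that rule does not secure the stratification factor. An unadjusted first step is ordinary reporting and is not in itself an error.

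Finally, the harm is small. This stands in full and sets the weight of the point.

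**Conclusion.** The point holds as a minor one. The stated rule makes no provision that the only stratification factor is in the primary comparison. If sex is prognostic and left out, the test is slightly conservative and the sHR is pulled slightly toward 1. The loss is about 0 to 1 point of power for a sex hazard ratio up to 2 and about 3 points at 3.

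Two stronger readings are not supported. Someone might infer that the unadjusted test has an inflated false-positive rate; the simulation shows none, and the direction is the opposite. Someone might also infer that the trial is undersized as a result; the 1068 reproduces without any sex term and does not change.

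The size of the effect rests on the assumed sex hazard ratios of 1 to 3 and on the simplified model. That the rule leaves adjustment for sex open rests on the text alone.

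**What to change.** State in the Statistics section, or in the analysis plan, that the primary mixed-versus-hard comparison and the other shoe comparisons include sex as a stratum or fixed covariate, regardless of its p value or the model fit. Report the unadjusted sHR as a supporting result. Keep the p<0.200 screen and the log-likelihood choice for the risk-factor analyses only.

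A stratum allows men and women different baseline curves. A fixed covariate is enough if the software's Fine-Gray routine does not offer strata.

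The cost is one sentence and one model term. Sample size, data collection and trial conduct do not change. It should be settled before the outcome data are analysed. Adding injury history from the baseline questionnaire as a pre-named covariate is optional and not needed to resolve this point.

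### The recruiter is shown each runner's coded group number under a fixed block of 12, so the next code is partly predictable; a unique shoe-pair number would remove this cheaply

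*Protocol article*

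**What the plan says.** All the elements are in the Methods of the protocol article, mostly under Stratified randomisation.

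- Allocation: "Participants will be randomised at a 1:1:1 ratio to one of the three treatment arms", and "A block randomisation (block size 12) will be performed". No other block size is mentioned, so each block holds four places per arm.
- Strata: "Randomisation will be stratified by sex, as the latter influences body mass". An independent statistician prepares two lists, one per sex, before recruitment opens.
- Participant ID: one digit for sex, "followed by three digits corresponding to the randomisation number".
- Information given to the recruiter: "the data collection system will provide the investigator in charge of the recruitment with a study group number for each participant". That investigator then enters a shoe number chosen by size and arm, and the system cross-checks it.
- Blinding: "The investigators in charge of the recruitment, the follow-up and data quality check, and the participants will be blinded regarding the shoe version distributed". Groups and shoes carry codes, and the shoe code is opened only once the analysis is finished.

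The Intervention section says the versions share one design and differ in cushioning by about 40% at the rear and 30% at the forepart, with an expected weight difference below 30 g at size 43.

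**The concern.** To hand over the right pair, the recruiter needs a shoe number. The procedure also shows which coded group each runner belongs to. With one fixed and published block size, and an ID that carries the list position, someone who has watched the earlier codes can work out what remains in the block.

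This matters at enrolment because some exclusions under Study population need judgement, for example contraindications to running, degenerative conditions, or a running injury in the preceding month. If the recruiter could foresee the next allocation and knew what the code stood for, enrolment could become selective.

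Knowledge of the codes could also weaken the assessor blinding that the article presents as a property of the trial under Study design and Limitations. The primary outcome is self-reported, and under Data collection staff phone non-responders and query inconsistent injury forms.

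**Working it through.** The article gives no figure for predictability, so there is none to reproduce. Its sample size serves here only as a multiplier, and it reproduces closely: 191 events for one pairwise comparison (HR 1.50, two-sided alpha 0.05, power 80%); 191 / 0.30 = 637 in two arms; × 1.5 = 956 in three; / 0.90 = 1063, against the stated 1068. The present point does not affect it.

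**Inputs from the article.** Three arms at 1:1:1; block size 12, hence 4/4/4; two lists by sex; N = 1068.

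**Assumptions not stated in the article.** (a) Randomisation numbers are issued in sequence and line up with the blocks. (b) Each arm has one code. (c) The observer sees every earlier code in the block.

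**Step 1: block position.** If numbering starts at 001, the position is ((number − 1) mod 12) + 1, which can be read from the ID.

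**Step 2: places known with certainty.** A place is certain when all places left in the block belong to one arm.
- 12th: always, 1.
- 11th: the last two places match, 3/11 = 0.2727.
- 10th: the last three match, 3/11 × 2/10 = 0.0545.
- 9th: the last four match, 3/11 × 2/10 × 1/9 = 0.0061.
- Sum: 1.333 per block, and 1.333 / 12 = 11.1%.

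**Step 3: places where at least one arm is ruled out.** Exact enumeration gives, for places 5 to 12: 0.006, 0.030, 0.091, 0.212, 0.418, 0.709, 1 and 1. The sum is 3.467 per block, or 28.9%.

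**Step 4: best guess.** The observer names the code with most places left. The probability of being right, for places 1 to 12, is 0.333, 0.364, 0.400, 0.412, 0.427, 0.459, 0.476, 0.497, 0.552, 0.588, 0.636 and 1. The sum is 6.144, and 6.144 / 12 = 51.2%, against 33.3% by chance.

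**Step 5: scale.** 1068 / 12 = 89 blocks. Certain: 89 × 1.333 = about 119 runners. At least one arm ruled out: 89 × 3.467 = about 309. The article says "the study population is expected to include about 40% of women", so the blocks split into 1068 × 0.4 / 12 = 35.6 female and 1068 × 0.6 / 12 = 53.4 male. Incomplete final blocks change the totals only slightly.

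**Step 6: would varying the block size help?** Naming the least-used code needs no knowledge of the block size, because the counts are level again after each block. The expected correct guesses are 3.367 in a block of 6, 4.787 in a block of 9 and 6.144 in a block of 12. With the three sizes equally likely, the rate is (3.367 + 4.787 + 6.144) / (6 + 9 + 12) = 14.298 / 27 = 53.0%, which is above 51.2%. Hidden varying sizes reduce the certain predictions of step 2, but sizes below 12 can raise the best-guess rate.

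**The case against.** The strongest reply is that every figure above concerns a code. Knowing that the next runner falls in group 2 gives no reason to enrol or turn away anyone unless the meaning of group 2 is known. This stands, and it limits the point.

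A reader might infer that handling one pair from each group reveals the code, so that one identified shoe unblinds a whole arm. The article does not support that as a fact. The shoes are anonymised and share one design. Stiffness is measured with a mechanical impact test, and nothing says it can be felt by hand. The weight figure is an expected upper limit at one size, with no direction by version. The number of codes per arm is not stated. Even with one code per arm, identifying a single code would leave the other two arms indistinguishable from each other.

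A reader might also infer that follow-up calls could differ by arm. The article gives the group number to the recruiting investigator, does not say that follow-up or data-quality staff see it, and states that they are blinded. The outcome comes from participants who are themselves stated to be blinded.

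Real safeguards exist: an independent statistician, lists fixed in advance, system-issued allocation and electronic cross-checking. Twelve is a fairly large block for three arms and two strata. The full protocol may also settle shoe labelling and when eligibility is locked. Releasing the number only after enrolment would still not stop prediction of later places in the block.

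**Conclusion.** The point holds as a moderate weakness in a stated procedure. Under assumptions (a) to (c), the next coded group is certain for about 11% of allocations (about 119 of 1068), at least one arm is ruled out for about 29% (about 309), and the best guess is right 51% of the time instead of 33%. If numbers are not sequential, if an arm has several codes, or if recruiters do not see each other's allocations, the figures would be lower.

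These counts are not numbers of biased enrolments. Harm requires the further step of decoding, which is plausible for someone who handles shoes differing in stiffness and possibly in weight, but is not demonstrated. The article therefore does not support a conclusion that blinding fails or that selection bias will occur, and the effect on the hazard ratio cannot be estimated from it. Severity is lower and confidence moderate. The point is worth acting on because the exposure is unnecessary and cheap to remove.

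**What to change.** 1. Record eligibility and shoe size in the system first. Then have it return only a unique shoe-pair number, with no group number on any recruitment or follow-up screen.
2. Run the cross-validation on the pair number. Keep the link from pair to arm with the independent statistician and the IT developer.
3. Take the participant ID from a counter separate from the randomisation number.
4. Optional: vary the block sizes and keep them undisclosed. As step 6 of the working shows, this reduces certain predictions but does not replace hiding the group number.

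The cost is a change to the system display, unique pair labels, a separate ID counter and stock catalogued by pair. Sample size, arms and comparisons are unchanged. Varying the block sizes would also mean regenerating the two lists. If recruitment has already begun, removing the group number from staff screens would still help for the remaining runners.

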### Data collection

Participants must fill in a baseline questionnaire to collect information regarding sociodemographic characteristics, running experience, training habits, running competitions performed and injury history. The intervention period will start as soon as the participants receive their study shoes and will last 6 months. During this intervention period, the participants are required to use the study shoes for all their running activities, to continue their usual training or follow their planned schedule and to fill out the weekly questionnaire on musculoskeletal problems, as well as on the use of the study shoes during the follow-up. Data on running practice will be downloaded from sports watches and their respective app via Strava in our dedicated electronic system. The system will collect the daily step count via Google Fit and the Apple Health mobile app. Information on using the study shoes will be collected via a weekly questionnaire. Data on cushioning perception will be collected three times using a dedicated questionnaire distributed when the runner has cumulated 5 hours and 25 hours of running and at the end of the intervention, respectively (online supplemental material 3).

Participants will be asked to complete a weekly questionnaire on any problem in the lower limbs or lower back region experienced during the previous 7 days (the Oslo Sports Trauma Research Centre (OSTRC) Overuse Injury Questionnaire).^27^ On top of the four basic questions, information regarding the following is required: date of symptom onset, sports discipline, anatomical location, type of injury, recurrence (ie, new, recurrent, exacerbation or subsequent injury), mode of onset and estimated return date to full participation (online supplemental material 4). Individual e-mail reminders will be sent to the participants who do not complete a weekly questionnaire. Personal phone calls will be made to participants who do not react to the e-mail reminders and if the reported information in the injury form is inconsistent. Study participation will be terminated, and the participant will be right-censored if he/she does not fill in the weekly injury form for two consecutive weeks, does not reply (or react) to the automatic reminders and cannot be reached by phone by the research team.

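### Runners who miss two weekly forms and cannot be reached are terminated and right-censored with no described way back, so injury follow-up stops where silence may itself be injury-related

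*Protocol article*

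**What the plan says.** All references are to the protocol article.

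- **Termination rule (Data collection).** "Study participation will be terminated, and the participant will be right-censored if he/she does not fill in the weekly injury form". A single missed form is not enough: the rest of the sentence sets the full condition, which is silence "for two consecutive weeks, does not reply (or react) to the automatic reminders and cannot be reached by phone by the research team". The three conditions must hold together.
- **Steps before termination (Data collection).** "Individual e-mail reminders will be sent to the participants who do not complete a weekly questionnaire", and, as a further step, "Personal phone calls will be made to participants who do not react to the e-mail reminders".
- **Recall window (Data collection).** The weekly form asks about "any problem in the lower limbs or lower back region experienced during the previous 7 days". It also requires "date of symptom onset, sports discipline, anatomical location, type of injury, recurrence" and an estimated date of return to full participation.
- **Running data (Data collection).** "Data on running practice will be downloaded from sports watches and their respective app via Strava in our dedicated electronic system".
- **Analysis (Statistics).** "Participants will be right-censored if lost to follow-up or at the end of the intervention period". The two sensitivity analyses deal with injuries in the first 2 weeks and with use of the study shoes. Neither deals with loss to follow-up.

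The article describes no way for a terminated runner to resume, and no later enquiry about injury.

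**The concern.** The primary outcome is a self-reported complaint that restricts or stops running for at least 7 days. A runner who has stopped because of pain, or who dislikes the shoe, may well stop answering a weekly running questionnaire. The rule responds to that silence by ending observation, and the analysis then treats the runner like any other censored participant. The Fine-Gray model needs censoring to be unrelated to injury risk. If silence is related to injury, that condition fails.

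Termination can occur once the first two forms are missed and contact has failed, with about 24 of roughly 26 weeks still to run. Nothing in the article makes termination necessary, because forms and reminders are electronic and running data come from the watch. A statistical analysis plan can model the data that were collected, but it cannot restore outcomes that the protocol stopped collecting.

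A second, smaller gap affects runners who stay in after missing forms. Their next form looks back only 7 days, so part of the interval since their last form may never be asked about.

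**Working it through.** **1. The plan's own figure.** Inputs from Sample size: alpha 0.05 (taken as two-sided, which reproduces the total), power 80%, HR 1.50, injury rate 30%, drop-out 10%. Three equal arms; the main comparison uses two of them.

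- Events needed = 4 × (1.96 + 0.842)² / (ln 1.5)² = 191.
- Participants in two arms = 191 / 0.30 = 637, or 319 per arm.
- With drop-out: 319 / 0.9 = 355 per arm, and 3 × 355 = 1065. The plan states 1068 (356 per arm), so its figure is reproduced.

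**2. Scale of the loss allowed for.** 10% of 1068 is about 107 runners. The article does not say how many of these would be lost through the termination rule.

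**3. Power of the main comparison.** Two arms hold 2 × 356 = 712 runners, and events = 712 × (1 − loss) × 0.30. Losses above 10% are assumptions. The formula counts no events at all from lost runners, which is pessimistic for those lost late.

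| Loss | Events | Power at HR 1.50 |
|---|---|---|
| 10% (planned) | 192 | 80.3% |
| 15% (assumed) | 182 | 78.0% |
| 20% (assumed) | 171 | 75.5% |

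Loss within the planned 10% is already covered by the sample size.

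**4. Effect on the HR.** As a crude approximation, recorded HR = 1.50 × (1 − f₁) / (1 − f₀), where f₁ and f₀ are the shares of injuries missed in the higher-risk and the other arm. All shares are assumed.

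| f₁ | f₀ | Recorded HR |
|---|---|---|
| 10% | 10% | 1.50 |
| 10% | 5% | 1.42 |
| 5% | 10% | 1.58 |

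Bias needs unequal loss, and it can go either way.

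**5. The 7-day window.** This assumes that missed forms are not filled in late and that the reminder or call does not itself collect the missing information; the article states neither. With k missed forms, 7k days are not covered by any completed form.

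- One missed form leaves 7 days. An episode wholly inside lasts at most 7 days, so apart from the boundary case only the shorter complaints of the secondary outcomes can be missed.
- Two missed forms leave 14 days. A primary injury of 7 to 13 days can then start and end unseen, provided the runner was reached and stayed in.
- An injury still present at the next form can be reported and dated back, because the form records symptom onset.

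**The case against.** The strongest defence is that the rule is not triggered lightly. A runner on holiday who answers one e-mail or one call stays in. Those terminated have failed three contact steps, and some would never answer again whatever the rule. The sample size allows for 10% drop-out. Participants are blinded to shoe version, which makes different rates of silence between arms less likely, though it does not exclude them. An article may also leave reinstatement, late entry and form logic to the full protocol, and the injury form and consent form are supplements that are not shown.

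Most of this stands, and it limits the point. The following stronger inferences are not supported:

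- **Two weeks of silence alone ends participation.** The reminder and phone conditions must also be met. Permanence is inferred from the rule and from the absence of a described way back; the article does not state it.
- **Injuries beginning in any gap are lost.** For a runner who resumes, onset dating recovers those still present. Only episodes fully resolved inside the gap are at risk.
- **Strava data could recover the injuries.** They can show that running stopped, but not why.
- **Hours run in missed weeks dilute incidence materially.** Time at risk is hours spent running, so a runner stopped by pain adds few or none.
- **The shoe HR is biased by a given amount, or power is lost.** Both rest on assumed shares.

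The defence does not remove the termination rule itself. The article states it outright, and on its wording outcome collection ends for these runners.

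**Conclusion.** The point holds in a limited form. For runners who miss two consecutive forms, do not react to reminders and cannot be reached by phone, the protocol ends participation and right-censors them, possibly early, with no described way to resume. That censoring may be informative, and outcome data that could still be collected at little cost are given up.

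The document does not allow the size or direction of any bias to be derived. If the same share of injuries is missed in both arms, the HR stays near 1.50; values such as 1.42 or 1.58 only illustrate assumed unequal loss. That silence is linked to pain or dislike of the shoe is plausible but also an assumption.

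The 7-day recall gap is secondary. It mainly concerns the short-duration secondary outcomes and reaches a primary injury of 7 to 13 days only after two missed forms. The change is worth making because it is cheap, not because serious bias has been shown.

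**What to change.** Replace termination by suspension:

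1. Keep the automatic weekly form, the reminders and the Strava feed active to month 6 unless consent is withdrawn.
2. Let a runner who answers again resume follow-up.
3. After any missed week, have the first form ask about problems since the last completed form, with onset and return dates.
4. Censor runners who never return at the last date covered by a completed form.

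The cost is protocol wording and a small change to form logic in the existing system, with no extra staff or visits. The consent wording should be checked to confirm that it covers continued contact. The downside is longer recall for the few runners who return after a gap. A closing form at month 6 for non-responders is optional: it could mean recall of up to about six months, and the change does not depend on it.
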